**Fig. 2 Fig2:**
[figure not shown]
Trial diagram

After approval of the Ethics Committee in Research of Shahid Sadoughi University of Medical Sciences (IR.SSU.SPH.REC.1399.135), a letter will be sent to the General Department of Education in Zahedan Province to obtain all elementary school lists and permission to conduct the research. The researcher will hold coordination meetings with school principals and explain the research clearly. During the COVID-19 prevalence, a specific application (the SHAD web) was developed by the ministry of education to be used for all schools for teaching, parental involvement, and other activities. Each school has this application. After the schools’ agreement, an announcement of the study will be posted on the schools’ channels. Online self-administered questionnaire will be provided to the target group through these school information channels (the SHAD web). Also, students’ written consent (electronically) is obtained before completing the questionnaire and documented in the experimental database. In addition to the consent of the students, the consent of the parents is also required. Thus, a link to an electronic consent form will be sent to parents. Parents who have agreed to the participation of their children send an electronic consent form to the researcher. After reviewing eligibility criteria, eligible students will complete baseline measures and then will be randomly divided into two groups (control and intervention) as detailed above and below.

### Randomization

The simple randomization will be done to assign participants for study groups by an independent statistician with a 1:1 allocation. A list of schools will be provided by referring to the Department of Education. Thus, Zahedan city will be divided into five education districts and randomly selected four schools from each district (one girl’s and boy’s school as the intervention group and one girl’s and boy’s school as the control group). A total of at least 20 elementary schools in Zahedan, with approximately 320 participants, will participate by simple randomization methodology. Once the students have consented and completed the baseline assessments, they will be randomized to intervention and control groups. From each school, the students selected will receive a special code through SPSS software, and after analyzing the data, they will be selected randomly through these codes. The independent statistician who has done the randomization informs the students by phone. Due to the nature of the intervention, it is impossible to blind participants and interventionists during the study. Still, outcome assessors will be blinded to group allocation in the final database as new identification numbers are assigned to participants. We will use the waiting-list control group design. After assessment T3, the control group will participate in the intervention program. This will be done so that both groups can experience the program. If participants withdrew or discontinued the educational intervention, researchers made efforts to encourage them to continue the study through two contacts. Also up to three text messages will be sent as reminders to complete questionnaires. Non-responders will be followed up by phone during the valuation period. Additionally, to increase adherence, digital notifications and reminders were sent to participants reminding them to visit and use the health messages, educational files, and skin cancer clip.

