### Description of study settings

This study is a randomized controlled trial (RCT) comparing intervention program with a control group in 10- to 12-year-old elementary school students. The project was implemented from April 2022 to July 2022. This period included participant recruitment, baseline data collection, and intervention (see Fig. 2). Randomization will be multi-stage random performed using a 1:1 (control: intervention) ratio. For this purpose, a list of elementary schools will be prepared. Thus, Zahedan city will be divided into five education districts and randomly selected four schools from each district (one girl’s and boy’s school as the intervention group and one girl’s and boy’s school as the control group). A self-administered questionnaire online will be provided to students through school information channels so that those who volunteer may participate in this research.

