### Sample size

The sample size is calculated to detect a minimum relative difference of 20% between both groups at post-assessment. This effect was based on the previous studies’ primary outcome and mean protection motivation scores. Based on the relevant literature [30], with alpha error at 0.05 and statistical power at 0.80, and protection motivation before mean ± SD (5.39 ± 2.17) and after mean ± SD (7.01 ± 1.75), ∆ = 2, *ρ* = 0.05, and *n* = 20 was estimated as 160 people. Therefore the total sample size is 320.

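### The protocol names simple randomisation, but also fixes a district-by-sex school layout that simple randomisation of 20 schools would give about 0.1% of the time; the unit and method must be reconciled

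*Protocol article*

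**What the plan says.** All references are to the protocol article.

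- **Method named.** The Randomization section states: "The simple randomization will be done to assign participants for study groups by an independent statistician with a 1:1 allocation". It later adds: "A total of at least 20 elementary schools in Zahedan, with approximately 320 participants, will participate by simple randomization methodology".
- **Layout of schools.** The same section says that "Zahedan city will be divided into five education districts and randomly selected four schools from each district", and specifies "one girl’s and boy’s school as the intervention group and one girl’s and boy’s school as the control group". Description of study settings gives the same layout.
- **A second name for the method.** Description of study settings says: "Randomization will be multi-stage random performed using a 1:1 (control: intervention) ratio".
- **Students as the unit.** The Randomization section also states: "Once the students have consented and completed the baseline assessments, they will be randomized to intervention and control groups". The end of Description of study settings likewise has eligible students complete baseline measures and only then be divided at random into the two groups.
- **Numbers.** The Sample size section "was estimated as 160 people. Therefore the total sample size is 320". It also prints ρ = 0.05 without saying what ρ is.

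**The concern.** Simple randomisation means an independent, unrestricted assignment of each unit. It guarantees neither a fixed number of units per arm nor a fixed number per stratum. The school layout guarantees both: in each district, each arm receives exactly one girls' school and one boys' school. A statistician who applies the named method to schools will break the layout. One who respects the layout will use a method that the protocol does not name.

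Two things are at stake. The first is reporting: readers judge a randomised trial partly on how the sequence was generated, and here the published description would not match the procedure. The second is balance: if the label were followed literally for schools, district and school sex could become entangled with treatment arm.

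Underneath lies a prior question. Schools appear to be assigned to arms, yet students are also said to be randomised individually after baseline. The right name for the method depends on which of these is the allocation.

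**Working it through.** **Inputs.** Five districts with four schools each; one girls' and one boys' school per arm per district; approximately 320 participants; 1:1 ratio (Randomization). Target of 160 per group (Sample size). "with alpha error at 0.05 and statistical power at 0.80" (Sample size); two-sided testing is assumed, because sidedness is not stated.

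**The plan's own counts.** 5 × 4 = 20 schools and 2 × 160 = 320 students; both agree with the text. The plan states no probability of balance. Whether its inputs lead to 160 per group is a separate question and does not bear on this point.

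**Step 1: schools as the unit.** Five districts × two sexes = 10 pairs of schools, and the layout requires every pair to split one and one.

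- Independent fair toss for each school: P(one pair splits) = 1/2, so P(all 10 split) = (1/2)^10 = 0.00098, about 0.1%.
- More generous reading, exactly 10 of the 20 schools drawn at random: 2^10 / C(20,10) = 1,024 / 184,756 = 0.0055, about 0.55%.
- Independent tosses give 10:10 overall with probability C(20,10) / 2^20 = 184,756 / 1,048,576 = 17.6%.
- A given district has all four schools in one arm with probability 2/16 = 1/8. At least one of five does so with probability 1 − (7/8)^5 = 49%.
- One of two schools drawn at random within each pair: the layout occurs with probability 1.

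These figures show that the label cannot describe the layout. They do not forecast what the trial will do.

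**Step 2: students as the unit.** With 320 independent fair tosses, the SD of an arm's size is √(320 × 0.25) = 8.9, and the 2.5th and 97.5th percentiles are 142 and 178. Exactly 160/160 has probability C(320,160) / 2^320 = 4.5%, but exact equality is not needed. Efficiency relative to equal arms is 4·n1·n2 / N². Power, if it is 80% at 160/160, is Φ[(1.960 + 0.842) × √efficiency − 1.960].

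| Split | Efficiency | Power |
|---|---|---|
| 160/160 | 1.000 | 80.0% |
| 150/170 | 4 × 150 × 170 / 320² = 0.996 | 79.8% |
| 142/178 | 4 × 142 × 178 / 320² = 0.987 | 79.5% |

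Even at the edge of the 95% range the loss is about half a power point.

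**Step 3: blocking by school, if students are the unit.** If ρ = 0.05 is the between-school correlation, the within-school share of variance is 1 − 0.05 = 0.95. Blocking by school and including school in the model then removes about 5% of the variance. This rests on a reading of ρ that the protocol does not confirm, and it requires the school term.

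**The case against.** The best defence is that the layout already is a restricted allocation. Description of study settings calls the process multi-stage, so nobody following the text would toss a coin for each of 20 schools. On this view the 0.1% models a procedure that the protocol does not describe, and only a label is wrong. Much of this stands: a restricted scheme is not absent, and the documents do not support an inference that the arms will be, or were, unbalanced on district or school sex. Two things remain. Simple randomisation is stated as the method, and the text does not say how the intervention school is chosen from each pair.

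A second defence is that simple randomisation refers only to participants, or to random selection into the study. The later sentence about schools and participants can be read as selection. The first cannot, since it concerns assignment to study groups. If it concerns students alone, it conflicts with schools having been placed in arms.

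A reader might also infer that the protocol promises 160/160 and that simple randomisation, giving it 4.5% of the time, fails that promise. The documents do not support this. The randomisation sections promise a 1:1 ratio and an approximate total; 160 is a target in Sample size. A balanced split inside each school is promised nowhere, and chance imbalance there does not bias an individually randomised comparison.

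**Conclusion.** The point holds for the allocation of schools. The named method and the described layout are incompatible: unrestricted assignment would give the layout about 0.1% of the time, or 0.55% if exactly ten schools were drawn. This result depends only on the protocol's counts of districts and schools.

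It does not extend to a general fault in simple randomisation. For students it is a valid 1:1 method, and its typical imbalance at 320 costs half a power point or less. Blocking within school would be a modest improvement, about 5% of variance, conditional on ρ being a between-school correlation and on school being in the model.

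Nor does renaming the method settle the matter alone. The contradiction over the unit comes first, because it decides which correction applies. The consequence is an inaccurate and unworkable description of sequence generation, not demonstrated bias. It is worth correcting because the description is central and the correction is small.

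**What to change.** State one unit of randomisation, in the same words, in Description of study settings and in Randomization. Then:

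- **If schools:** replace both mentions of simple randomisation with allocation stratified by district and school sex. Within each district, one of the two girls' schools and one of the two boys' schools is drawn at random for intervention. Reflect the strata and the clustering by school in the analysis, and remove the statement that students are randomised individually after baseline.
- **If students:** simple randomisation may stay, and the text placing whole schools in arms must go. Permuted blocks of varying size within school, with school in the model, are an inexpensive option. Define ρ so that the gain can be judged.
- **If allocation has already taken place:** describe the method actually used and analyse accordingly. Description of study settings reports in the past tense a project run from April to July 2022, while the dates in Trial status conflict, so the documents do not settle whether this applies.

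The cost is a few corrected sentences, a different list-generation step if allocation is still ahead, and matching terms in the model. No extra students, staff or data are needed.

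### The protocol gives two incompatible accounts of what is randomised and when: schools labelled by arm at selection, or individual students after baseline

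*Protocol article*

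**What the plan says.** The Protocol article describes allocation in several places.

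- **Description of study settings.** The city is divided into five education districts, with "randomly selected four schools from each district (one girl’s and boy’s school as the intervention group" and a corresponding pair as control. The same paragraph states: "Randomization will be multi-stage random performed using a 1:1 (control: intervention) ratio".
- **Description of study settings, text after Fig. 2.** After the eligibility review, "eligible students will complete baseline measures and then will be randomly divided into two groups (control and intervention").
- **Randomization.** The section opens with "The simple randomization will be done to assign participants for study groups by an independent statistician with a 1:1 allocation". It then repeats the school layout: "one girl’s and boy’s school as the intervention group and one girl’s and boy’s school as the control group". Two sentences later it says "Once the students have consented and completed the baseline assessments, they will be randomized to intervention and control groups". Next it gives students in each school a code and says "after analyzing the data, they will be selected randomly through these codes".

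Three other sections bear on the point. Questionnaires places T1 before randomisation. Sample size lists ρ = 0.05 and n = 20 without saying what either denotes. Data analysis specifies linear mixed models for the repeated measures and names no school term.

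**The concern.** A student in a school labelled control cannot also be allocated 1:1 to either arm after baseline. One of the two accounts must be wrong, and the choice between them changes the trial.

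- **If schools are the unit,** this is a cluster-randomised trial. The labels are attached when schools are selected, and the announcement, volunteering, consent and baseline are described as coming later. T1 may then not precede randomisation, and differential volunteering by arm becomes possible. Outcomes of students in one school are correlated, so the analysis has to include school.
- **If students are the unit,** schoolmates are split between arms in a trial where participants cannot be blinded and the content arrives as WhatsApp messages that are easily passed on. Contamination is a risk, and it would tend to dilute the group difference.

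This goes beyond detail that a condensed article leaves out. The unit is stated twice, in opposite ways, within one section.

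**Working it through.** **1. The two accounts side by side**

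| | School account | Student account |
|---|---|---|
| Where | Description of study settings; Randomization | Text after Fig. 2; Randomization |
| What sets the arm | The label given to the school | Random assignment of each student |
| When | At selection of schools | After consent and baseline |
| Layout | 5 districts × 4 schools = 20 schools, 10 per arm | Simple 1:1 |

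Two reconciliations can be tried.

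- Schools carry the arm and students are only sampled within them. The term multi-stage and the code sentence allow this. The two sentences that randomise students to intervention and control after baseline do not.
- Schools are only a sampling frame. The student sentences allow this. The arm labels on schools do not.

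Neither survives the whole text.

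**2. Does the sample size settle it?**

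Inputs from Sample size: alpha 0.05 (taken as two-sided), power 0.80, SDs 2.17 and 1.75, Δ = 2, a 20% relative difference, ρ = 0.05, n = 20, result 160 per arm.

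Pooled SD = √((2.17² + 1.75²)/2) = 1.971. Per-arm n = 2 × (1.960 + 0.842)² × 1.971² / d², rounded up. The last column multiplies by 1 + 19 × 0.05 = 1.95, reading n = 20 as cluster size.

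| Effect d | n per arm | × 1.95 |
|---|---|---|
| 2 (stated Δ) | 16 | 32 |
| 1.62 (7.01 − 5.39) | 24 | 47 |
| 1.402 (20% of 7.01) | 32 | 63 |
| 1.078 (20% of 5.39) | 53 | 104 |

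None of these gives 160. A ρ of 0.05 with n = 20 would suit a clustered design, but the section does not say so and its result cannot be used to infer the unit. The failure to reproduce 160 is a separate matter.

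**3. What the unit changes**

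Assumptions: ρ is the intracluster correlation (ICC), and there are 320/20 = 16 students per school.

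- School allocation: design effect 1 + (16 − 1) × 0.05 = 1.75; effective n = 160/1.75 ≈ 91 per arm.
- Student allocation: design effect about 1.

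If schools are allocated and school is left out of the model, the true two-sided error is 2 × (1 − Φ(1.960/√DE)):

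| ICC | DE | 1.960/√DE | True error at nominal 5% |
|---|---|---|---|
| 0.01 | 1.15 | 1.828 | 6.8% |
| 0.02 | 1.30 | 1.719 | 8.6% |
| 0.05 | 1.75 | 1.482 | 13.8% |
| 0.10 | 2.50 | 1.240 | 21.5% |

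**4. Power**

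For a difference of 1.078 with SD 1.971, the normal approximation gives about 99.8% with 160 per arm and about 95.9% with an effective 91 per arm. Power is not where the harm lies.

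**The case against.** The best defence is that the text is badly worded but coherent. The scheme is called multi-stage, the sentence after Fig. 2 refers the reader to the description above and below it, and the code sentence can be read as sampling students within schools. Schools would then carry the arm. Fig. 2 itself is not available to check. This reading is plausible, but it requires the sentences that randomise students after baseline to mean something else, so the text still has to be corrected.

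The defence does rule out several stronger inferences that a reader might draw.

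- **That the allocation is unworkable.** Either procedure alone is feasible. Only the combined text cannot be followed.
- **That students volunteered knowing their arm.** No section says a school's arm is disclosed. The independent statistician informs students by phone, which is described after consent, baseline and randomisation. Differential volunteering is a possibility, not something shown.
- **That data steer who is included.** The code sentence still says selection is random, and the analysis it mentions may be the eligibility review. It is unclear wording, not evidence of data-driven selection.
- **That simple randomisation of 20 schools would rarely give the stated balance.** The section applies simple randomisation to participants. No independent coin toss per school is clearly planned.
- **That an ICC of 0.05 is the protocol's own figure.** The symbol is unlabelled, so a range is needed.

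**Conclusion.** The contradiction stands: the current text gives two units and two times of randomisation, and no section reconciles them. Its consequence is conditional.

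Under school allocation, T1 may not be a pre-randomisation baseline. With an ICC of 0.05 and 16 students per school, a model without school would run at about 13.8% two-sided error instead of 5% (6.8% to 21.5% for ICCs of 0.01 to 0.10). That figure rests on an assumed ICC, equal school sizes, a large-sample approximation and school being omitted, which the Data analysis section neither says nor rules out. Under student allocation the design effect largely disappears and contamination takes its place. Power for a 20% difference stays high either way.

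**What to change.** State one unit and one time of randomisation, and make Description of study settings (including the text after Fig. 2), Randomization and Questionnaires agree.

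- **If school is the unit,** which fits the arm-labelled schools: call it a cluster-randomised trial stratified by district and school sex (5 × 2 = 10 strata, two schools each if there are exactly 20). Delete the simple randomisation of participants. If allocation is still open, allocate within each stratum only after consent and T1 are closed in both of its schools. Add a school random effect, a small-cluster correction and the stratification factors to the mixed model.
- **If students were randomised:** remove the arm labels from schools, state that schools are only the sampling frame, and acknowledge contamination.
- **If allocation has already taken place:** the settings section puts implementation in April to July 2022, in the past tense. State which procedure was used and match the analysis to it.
- **In every case:** reword or delete the sentence that selects students by code after data are analysed.

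The cost is mostly wording. The school design brings a wait for T1 to close and wider confidence intervals: by √1.75 ≈ 1.32 at an ICC of 0.05, before the small-cluster correction.

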### Outcomes

Data collection from demographic information to measuring sun protection behavior, and PMT constructs including perceived vulnerability, perceived severity, response effectiveness, self-efficacy, reward, perceived response cost, fear, and protective motivation in students will be done with an online self-administered questionnaire. Figure 6 provides a SPIRIT depiction of the schedule of enrollment, interventions, and assessments**.**

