### Questionnaires

Data will be collected through a self-administered questionnaire at three points: (T1) pre-randomized baseline, (T2) immediately after the intervention, and (T3) 3-month follow-up. All participants will complete a questionnaire that includes socio-demographic characteristics, sunscreen behavior, and PMT constructs.

Socio-demographic characteristics include age, gender, educational level, and parents’ jobs.

Sun protection behaviors will be measured through 7 questions: three questions about using sunscreen and four questions about other protective behaviors, including wide-brimmed sun hat, sunglasses, clothing, and shade-seeking.

The PMT constructs include susceptibility, severity, response efficacy, self-efficacy, reward, perceived response cost, fear, and protection motivation.

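### The protocol calls outcome assessors blinded, but every outcome is self-reported by students who know their group; renumbering the database can mask only data handlers or analysts

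*Protocol article*

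**What the plan says.** The Randomization section of the protocol article makes four relevant statements.

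- On participants and staff: "Due to the nature of the intervention, it is impossible to blind participants and interventionists during the study".
- In the next sentence, as a counterweight: "outcome assessors will be blinded to group allocation in the final database". The means given is that participants receive new identification numbers.
- On how students hear of the result of randomization: "The independent statistician who has done the randomization informs the students by phone".
- On the comparator: "We will use the waiting-list control group design". Controls are offered the programme after T3.

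On measurement, the Outcomes section says that data collection on behaviour and on all PMT constructs "will be done with an online self-administered questionnaire". The Questionnaires section repeats this for baseline, T2 and T3: "Data will be collected through a self-administered questionnaire at three points". The Primary outcome and Secondary outcomes sections name the same nine parameters, at T2 and T3 respectively: sun protection behaviour and eight PMT constructs. The article describes no observed, device-based or interviewer-rated outcome.

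**The concern.** In a trial with self-administered questionnaires, the respondent is the person who assesses the outcome. Here that is a child aged 10 to 12 who either received the programme or is waiting for it. The protocol says this child cannot be blinded, yet it presents outcome assessment as blinded.

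What is at stake is how the result is read. A blinded assessor protects against answers or ratings shifting because the group is known. Nothing in this design gives that protection, and several features make such a shift plausible:

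- The control is a waiting list, and no attention or sham condition is described.
- According to the Procedure section, the T2 and T3 questionnaires are completed inside the WhatsApp programme set up to deliver the intervention.
- The app described under Interventions asks seven behaviour questions, then shows an altered face and gives recommendations according to the score. The behaviour outcome is also seven questions, with the same split of topics (three on sunscreen, four on shade, hat, clothing and sunglasses). Intervention students are thus shown which answers are desirable on closely matching content.

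A reader who relies on the blinding sentence could rate the risk of bias in outcome measurement lower than the design warrants. The Limitations section would not correct this, since it discusses only the pandemic.

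**Working it through.** The blinding statement rests on no sample size or power figure, so there is no planned number to reproduce. The check matches each outcome to the person who records it and to that person's blinding status.

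**Step 1. Who rates each outcome**

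| Outcome set | Measures | Rated by | Rater blinded? |
|---|---|---|---|
| Primary, T2 | 1 behaviour + 8 PMT constructs = 9 | Student, self-administered online | No |
| Secondary, T3 | the same 9 | Student, self-administered online | No |

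Measures with a separate assessor: 0 of 9 at T2 and 0 of 9 at T3.

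**Step 2. When the masking acts**

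The order of events is allocation, phone call, intervention or waiting list, questionnaire, final database, new identification numbers. The numbers are attached to answers already given. They can change what a data handler or analyst knows, but not what the student knew when answering.

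**Step 3. Illustration of what unblinded self-report can do**

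This step is illustrative only. The documents give no size for a reporting shift, so a range is assumed.

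Inputs: 160 per arm (Sample size section) and alpha 0.05 (Data analysis section; two-sided is assumed, as the article does not say). The true effect is set to zero, and the intervention arm's answers shift by b standard deviations (SD).

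Formula, in SD units: SE = sqrt(2 × DEFF / 160), where DEFF is the design effect. For a z-test, P(p < 0.05) = 1 − Φ(1.96 − b/SE) + Φ(−1.96 − b/SE).

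- No clustering: DEFF = 1, SE = sqrt(2/160) = 0.112.
- Sample size section's ρ = 0.05 read as an intraclass correlation and n = 20 as cluster size: DEFF = 1 + 19 × 0.05 = 1.95, SE = sqrt(3.9/160) = 0.156.
- 20 schools of 320/20 = 16 students, same correlation: DEFF = 1 + 15 × 0.05 = 1.75, SE = sqrt(3.5/160) = 0.148. Here a between-school t-test with 18 degrees of freedom is used (noncentral t).

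| Assumed shift b | DEFF 1, z | DEFF 1.95, z | DEFF 1.75, t with 18 df |
|---|---|---|---|
| 0.1 SD | 14.5% | 9.8% | 9.8% |
| 0.2 SD | 43.2% | 24.9% | 24.9% |
| 0.3 SD | 76.5% | 48.5% | 48.4% |

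Each entry is the chance of a significant result on one outcome with no true effect. Renumbering the database changes none of them.

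**The case against.** The strongest reply is that this is a labelling error in an otherwise open document. The full sentence on assessors says how the masking is done and places it in the final database, so it describes a data-handling measure. The sentence before it admits that participants are unblinded, and several sections state that the questionnaires are self-administered. Nothing is hidden. Eight of the nine parameters are internal states, such as fear and self-efficacy, that no outside assessor could rate. The conclusions in the Abstract and Discussion are conditional.

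Much of this stands, and it rules out three stronger readings that a reader might infer.

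- **That no protection of any kind exists.** The documents do not support this. Renumbering may give real masking at the handling or analysis stage. What it cannot give is blinded measurement.
- **That school codes defeat even the analyst masking.** This would follow only if whole schools belong to one arm and the analysis file identifies the school. The study settings text and part of the Randomization section assign schools to arms. Elsewhere both sections say that students are randomized after consent and baseline. No section places a school variable in the masked database, and the Data analysis section names no school term.
- **That the percentages above measure the harm of this sentence.** They rest on an assumed shift and on simple tests, whereas the plan is a linear mixed model. They would apply to any open trial with self-reported outcomes, and rewording the sentence would not alter them.

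What does not stand is the suggestion that the sentence can remain. It claims blinding for a role that, in this design, only the unblinded student fills.

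**Conclusion.** The statement is wrong as written. All nine primary and all nine secondary measures are self-reported by students who know their group, so outcome assessment is not blinded. The measure described can at most blind those who handle or analyse the data. This conclusion needs no numerical assumption and holds whether schools or students are the unit of allocation. The illustrative percentages are not part of it.

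The consequence is limited but touches every endpoint: the trial can support conclusions about self-reported behaviour and beliefs under open allocation. Self-report is not itself a fault here, and the article nowhere claims observed behaviour. The article should be corrected because it credits the design with a safeguard it lacks. The correction is cheap.

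**What to change.** 1. In the Randomization section, replace the sentence on assessors with wording such as: Outcomes are self-reported by participants who know their allocation, so outcome assessment is not blinded. The data analyst will be blinded: arm labels, and any variable that reveals the arm, will be masked until the database and the analysis model are locked.
2. If whole schools are allocated to one arm and a school code is kept in the analysis file, treat that code as one of the variables to mask.
3. In the Abstract's discussion paragraph and in the Discussion section, word the conclusions as concerning self-reported sun-protective behaviour and PMT scores under open allocation.
4. Add unblinded self-report to the Limitations section.

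The cost is a few sentences and recoded identifiers in the analysis file. Outcomes, sample size, analysis model and conduct are unchanged. The design will look slightly less favourable on paper.
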